### 3.1.2 Implications of relative plasma volume status in heart failure

#### 3.1.2.1 *Relative plasma volume status and clinical outcomes in heart failure*

The relative plasma volume status (PVS) is a parameter that reflects the relative deviation of the actual plasma volume (aPV) from the calculated ideal plasma volume (iPV) of a person.

The aPV can be either estimated (ePV), e.g. by the 'Hakim' formula [36], which is based on the actual subjects hematocrit, body weight and sex-dependent constant factors or measured (mPV), e.g. by use of the optimized CO rebreathing (OpCO) technique. The iPV is calculated using a well-established formula based on body weight and on a sex-dependent constant factor.

The PVS has been recently shown to be predictive for clinical outcomes [9, 10, 37]. For example, Ling et al. showed that the PVS was associated with morbidity and mortality in a large cohort (more than 5000 patients of the Valsartan in Heart Failure Trial, Val-HeFT) of HF patients with reduce ejection fraction (HFrEF) [9].

Furthermore, Grodin et al. [37] found that the PVS was independently associated with long-term clinical outcomes (e.g. all-cause mortality and HF hospitalization) in a large cohort (more than 3000 patients) of HF patients with preserved ejection fraction (HFpEF).

Martens et al. [10] reported that a higher PVS was independently associated with a higher risk for HF hospitalization and all-cause mortality in a large cohort of HF patients with mixed (HFrEF, HFmrEF, HFpEF) ejection fractions. Interestingly, the hazard ratio ( $H_R$ ) plot for HF hospitalization and all-cause mortality against PVS showed a J-shape curve (Fig. 6) with a prominent incline in  $H_R$  starting at a PVS value of +2% percent and at > -20% on the negative scale in relation to iPV. The graphical illustration also reveals that above a PVS of +2% every additional 2% increase is associated with an increase in the event  $H_R$ . The same authors also reported that the calculated 'optimal' PVS defined as PVS with lowest event  $H_R$  is a slightly contracted (-6.5%) volume status in comparison to the calculated iPV (Fig. 6).

Additionally, Kobayashi et al. found that the estimated PVS at hospital discharge was independently associated with post-discharge clinical outcomes (e.g. re-hospitalization, worsening of HF or all-cause mortality) in 3 cohorts of patients admitted for ADHF. The estimated PVS in this study was calculated by use of the 'Strauss formula', which is based on actual hematocrit levels and hemoglobin concentrations of the patients.

Also, in patients undergoing coronary artery bypass graft surgery (CABG) a higher PVS was associated with worse inpatient outcomes after CABG [38].

In summary, the PVS clearly seems to have important prognostic implications in chronic HF patients with mixed ejection fractions and also in hospitalized acute decompensated (congestive) heart failure

(ADHF) patients. Thus, therapies that improve the PVS towards 'euvoemia' (PVS= 0, or slightly below) by shifting the actual plasma volume (aPV) closer to ideal plasma volume (iPV) may improve clinical outcomes in HF patients in general but in ADHF patients in particular.

[figure not shown]

**Fig. 6: Relationship between plasma volume status and risk of heart failure hospitalization and all-cause mortality is J-shaped.** The blue square indicates the optimal plasma volume divergence interval without an increase in hazard ratio (HR) for HF-hospitalization and mortality (adapted and modified from Martens et al. [10]).

### 3.1.2.2 Relative plasma volume status measured with the optimized CO-rebreathing technique

The plasma volume (PV) will be measured by use of the OpCO technique to calculate the PVS as the primary outcome variable. Although the OpCO technique is not yet established in clinical routine it is a highly accurate and reliable method as reflected by a reported low typical error (TE, 1-2%) and coefficient of variation (CV, 2.2%) for measuring total haemoglobin mass ( $Hb_{mass}$ ), the basis to calculate intravascular volumes [39-41].

The safety and feasibility of the OpCO technique in HF patients, even in those with a severely reduced left ventricular function as indicated by a very low (< 40%) LVEF have been recently proven [42].

Furthermore, the recent applications of the OpCO technique to measure blood- and plasma volumes in patients with chronic kidney disease [43], dialysis-dependent kidney failure [44, 45] and in patients with chronic liver disease [46] further emphasizes the feasibility of applying OpCO technique in the clinical setting and also shows the brought ranged potential of this technique in the clinics.

Additional validation studies that compare the OpCO technique with other gold standard methods are currently ongoing (internal communication with Detalo Healths company, unpublished data). A direct comparison between the estimated PV (ePV) assessed by the Hakim formula [36] and the measured PV (mPV) by OpCO technique to calculate the PVS has not yet been performed.

However, a recent study performed by Martens et al. [10] could demonstrate that the measured PV in HF patients by use of a radioactive isotope (technetium-99) red blood cell (RBC) labelling technique correlated well with the estimated PV as calculated by the Hakim formula.

In this context, Gore et al. [39] could further show in a meta-analysis that the measurement error of CO-rebreathing is comparable (even lower) to radioactive RBC labelling technique. Thus, we think that the measured PV by use of OpCO technique will reflect well the estimated PV based on the 'Hakim' formula.

Actually, we think it may reflect 'true' PV levels in HF patients more accurately than with the 'Hakim' formula as it's based on the direct measurement of volume independent  $Hb_{mass}$  (for further details see also 9.2.1) and not solely on concentration dependent measures (e.g. Hct).

Nevertheless, we will compare (correlate) the PVS obtained from the 2 different approaches with each other. Importantly, the OpCO technique is in contrast to radioactive isotope labelling techniques relatively easy to apply and fast (results within 15 minutes), and does not expose patients to radiation.

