Thus, the measured PV by use of OpCO technique (see formulas below) should reflect well the estimated PV based on the Hakim formula. Actually, it may reflect 'true' PV levels more accurately as it's also based on the direct measurement of volume independent total haemoglobin mass ( $Hb_{\text{mass}}$ , see formula below) and not solely on concentration dependent measures (e.g. Hct). Nevertheless, we will compare (correlate) the 2 different PV estimations with each other.

The underlying formulas used by us [45] and others [44] to calculate blood volume using OpCO technique are as follows:

- 1)  $nCO_{\text{absorbed}} = P_{\text{atm}} \times VCO_{\text{absorbed}} / (R \times T)$ ;
- 2)  $nHb_{\text{tagged}} = nCO_{\text{absorbed}} / 4$ ; (1 mole Hb binds 4 moles CO);
- 3)  $nHb_{\text{total}} = (nHb_{\text{tagged}} / \Delta HbCO) \times 100\%$ ;

- 4)  $Hb_{mass} = nHb_{total} \times 6.44 \times 10^4 \text{ g/mol}$  (= molar mass of Hb);
- 5)  $RBCV = Hb_{mass} \times Hct / Hb$ ;
- 6)  $BV = RBCV / Hct$ ;
- 7)  $PV \text{ (mPV)} = BV - RBCV$ ;

\*Hct should be corrected to whole-body Hct by the factor 0.91 [94].

Abbreviations:  $nCO_{absorbed}$ : amount of absorbed CO in moles after CO-rebreathing,  $P_{atm}$ : atmospheric pressure,  $VCO_{absorbed}$ : absorbed volume of CO in liters,  $R$ : gas constant (0.08206 l atm / (mol·K)),  $T$ : room temperature in Kelvin,  $nHb_{total}$ : total amount of Hb in moles,  $nHb_{tagged}$ : amount of tagged Hb in moles,  $\Delta HbCO$  (%): difference in carboxyhemoglobin (HbCO) measured in venous blood samples pre- and post CO-rebreathing,  $Hb_{mass}$  (g): total hemoglobin mass,  $RBCV$  (l): red blood cell volume,  $BV$ : blood volume,  $mPV$ : measured plasma volume;

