#### **11.4.2 Primary Analysis**

For the primary analysis, a mixed model for repeated measures (MMRM) - will be applied for continuous outcome variables (e.g.  $\Delta$ PVS) to test for a potential treatment effect between groups (DAPA vs. PLA).

**Rationale:** Although the ANCOVA test is considered as statistical 'robust' and 'efficient' test for analysing continuous outcomes requiring covariate adjustment in RCTs [121] and was previously used by others in a comparable study setting [122]. However, the MMRM has the advantage to better handle missing data at random and thus avoids to 'lose' subjects in the data analysis.

For testing of potential associations between outcome variables Pearson's correlation coefficient ( $r$ ) will be used or if case of non-normal distributed data the Spearman's rank correlation coefficient ( $\rho$ ) will be used. A p-value of  $< 0.05$  is considered to indicate statistical significance.

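### CO-rebreathing and formula-based plasma volume are to be compared by correlation alone, which cannot show whether the two agree in level

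*Protocol*

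**What the plan says.** Section 3.1.2.2 states that CO-rebreathing (OpCO) plasma volume has not been compared directly with the Hakim estimate, and gives the expectation: "Thus, we think that the measured PV by use of OpCO technique will reflect well the estimated PV based on the 'Hakim' formula". It then names the method: "Nevertheless, we will compare (correlate) the PVS obtained from the 2 different approaches with each other". Section 9.2.1.2 repeats both steps for plasma volume. The measured value "should reflect well the estimated PV based on the Hakim formula", and "Nevertheless, we will compare (correlate) the 2 different PV estimations with each other". No mean difference, limits of agreement, concordance measure or acceptable difference is given in either place.

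Section 11.4.2 sets the general rule for associations: "For testing of potential associations between outcome variables Pearson's correlation coefficient", or Spearman's coefficient for non-normal data, with p < 0.05 as the threshold.

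The inputs overlap. Section 3.1.2.1 describes the formula estimate as one "which is based on the actual subjects hematocrit, body weight and sex-dependent constant factors", and adds: "The iPV is calculated using a well-established formula based on body weight and on a sex-dependent constant factor". That ideal volume (iPV) is the denominator of PVS by either method (9.2.1.1, 9.2.1.2). The OpCO plasma volume also uses haematocrit, corrected by a factor of 0.91 (9.2.1.2).

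**The concern.** Whether a measured value reflects a formula value is a question about level: how far apart the two are, and whether the gap changes with size. A correlation coefficient answers a different question, namely whether patients rank or line up similarly. Two methods can differ by 20 points in every patient and still correlate perfectly.

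The overlap of inputs adds a second problem. Because each PVS value contains a haematocrit term and is divided by the same iPV, the two correlate to some degree whatever the OpCO device contributes.

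What is at stake is the absolute PVS level. The secondary outcome %PVSopt (5.2) counts patients between -4% and -18%, an interval taken from published PVS studies; 9.2.1.2 describes one of its two sources as having used the Hakim formula. In this trial the interval is applied to PVS measured by OpCO. A systematic offset would change who falls inside it, and the planned comparison would not show the offset.

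**Working it through.** The protocol gives no figure for this comparison. The only design number used below is the 80 patients of section 11.2, which is not disputed.

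**Step 1. The two quantities, from 9.2.1.1 and 9.2.1.2.**
- Formula: ePV = (1 - Hct) x V, with V = a + b x weight (a = 1530, b = 41 in men; a = 864, b = 47.9 in women).
- Measured: mPV = BV - RBCV. With the 0.91 correction this is mPV = BV x (1 - 0.91 x Hct).
- Both: PVS = 100 x (PV / iPV - 1), with iPV = c x weight (c = 39 in men, 40 in women).

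For PVS, the shared parts are the haematocrit term and the denominator iPV. Since iPV is only a constant times weight, weight and iPV count as one shared source. For PV itself, weight does not enter the OpCO formula, so only haematocrit is shared algebraically.

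**Step 2. Offset from the 0.91 factor alone.** Assume a man of 80 kg with Hct 0.39, and let both methods see the same blood volume.
- V = 1530 + 41 x 80 = 4810 ml; iPV = 39 x 80 = 3120 ml.
- Formula: 0.61 x 4810 = 2934 ml, so PVS = 100 x (2934 / 3120 - 1) = -6.0%.
- OpCO form: 1 - 0.91 x 0.39 = 0.6451; 0.6451 x 4810 = 3103 ml, so PVS = -0.5%.
- Shift: 100 x 0.09 x 0.39 x 4810 / 3120 = 5.4 points.

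The interval is 18 - 4 = 14 points wide. This patient is inside it by the formula and outside it by the OpCO form, although the blood volume is identical.

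**Step 3. Correlation does not register offset or scale.** For any constant k and positive multiplier m, the correlation of X with k + mY equals that of X with Y. Simulated at n = 80, with OpCO blood volume set to a multiple of V plus 8% noise:

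| Multiple of V | Mean r (PVS) | Significant at 0.05 | Mean PVS difference (points) |
|---|---|---|---|
| 0.8 | about 0.77 | 100% | -15 |
| 1.2 | about 0.77 | 100% | +25 |
| 1.4 | about 0.77 | 100% | +45 |

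A true association is built into these runs, so the 100% is power and not false positives. The table shows that r stays the same while the disagreement changes sign and triples in size.

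**Step 4. Correlation from shared terms alone.** Here the quantity that only OpCO supplies is drawn at random, unrelated to the patient's formula value beyond what the row states. Assumed, and not in the protocol: 70% men, mean weight 85 kg (men) and 72 kg (women) with SD 18, mean Hct 0.38 with SD 0.04 to 0.06, CV of the random quantity 10% to 25%. Two-sided Pearson test, n = 80:

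| Random quantity | Mean r (PVS) | Significant |
|---|---|---|
| Haemoglobin mass | 0.69-0.89 | 100% |
| Blood volume | 0.53-0.73 | 99.8-100% |
| Haemoglobin mass per kg | 0.37-0.74 | 93-100% |
| Blood volume per kg | 0.16-0.53 | 28-100% |

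The last row is the least favourable, because only haematocrit is then effectively shared; a rerun of its low end gave about 27%. Spearman rates are nearly the same. For PV the inflation is weaker: with haemoglobin mass random (600 g, CV 20% to 30%, weight 80 ± 16 kg, mean Hct 0.39 with SD 0.04 to 0.05), 43% to 87% of trials were significant.

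**Step 5. What an agreement analysis shows.** In the simulated data of step 4, the mean difference was about +22 to +27 PVS points, the limits of agreement were about ±26 to ±92 points around it, and the concordance coefficient was 0.06 to 0.31. The disagreement is plain in data where the correlation test usually rejects.

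**The case against.** The strongest reply is that the protocol commits to little here. Neither sentence states a null hypothesis, a p-value, an acceptance criterion or a decision that depends on the result. The p < 0.05 rule in 11.4.2 concerns associations between outcome variables, and formula-based PVS is not a listed outcome, so a purely descriptive r fits the text equally well. The endpoint uses the measured volume whatever the comparison shows. Its justification is the reported typical error of 1-2% and CV of 2.2% for haemoglobin mass, and 3.1.2.2 considers OpCO possibly closer to the truth than the formula. All of this stands.

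A reader might infer that a significant r is certain and would be taken to validate the primary endpoint. The documents do not support either half. The protocol nowhere says that r will validate anything. The rejection rate also depends on how the absence of a link is modelled, and falls to roughly 30% in the least favourable case. The simulations with random OpCO input are stress tests too, far from the reported measurement error.

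It can also be said that details of a method comparison belong in a statistical analysis plan, which is not shown. That would answer a missing detail. Here the protocol names the method twice, and the method does not fit the question it sets.

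**Conclusion.** The point holds as a limited one. Correlation is the only method named for a question of agreement; it cannot detect an offset or a difference in scale, and for PVS it is inflated by shared haematocrit and a common denominator. The blindness to offset is algebraic and needs no assumption. The inflation rates (about 30% to 100% at n = 80) and the 5.4-point shift rest on assumed patient values.

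It is a side analysis. The randomised comparison uses measured PVS in both arms, so neither that comparison nor the sample size is affected. The consequence is confined to the absolute PVS level: %PVSopt, and how far published formula-based evidence can be carried over to OpCO values. A change is worth making because it is cheap and the data are already collected.

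**What to change.** In 3.1.2.2 and 9.2.1.2, replace the planned correlation with an agreement analysis of the paired values:
- mean difference (OpCO minus formula) and 95% limits of agreement, each with confidence intervals, for PV in ml and PVS in percentage points at baseline;
- a check for proportional bias, such as regressing the difference on the mean of the two methods;
- the same analysis for change from baseline to week 12.

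Keep r as a descriptive figure, and state that no conclusion on interchangeability will be drawn from it or its p-value.

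The cost is a wording change, one table and one plot, from haematocrit, weight, sex and OpCO data already collected. The downside is that the result may show poor agreement, which would then have to be discussed when %PVSopt is interpreted.

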### 3.1.3 SGLT-2is and cardioprotection in heart failure- a 'volume-based' perspective

#### 3.1.3.1 *SGLT-2is- from diabetes to heart failure with and without kidney disease*

Originally designed to treat diabetes, the sodium-glucose-co-transporter 2 inhibitors (SGLT-2is), which are gathered under the term 'gliflozins', were proven in several large controlled trials to be cardio- and also reno-protective [47].

For example, the study results of the EMPA-REG OUTCOME trial with more than 7000 enrolled patients revealed that the SGLT-2i empagliflozin substantially reduced the risk (in comparison with placebo) of major adverse cardiovascular events, cardiovascular (-38%) and all-cause death (-32%) as well as hospitalization for heart failure (-38%) in patients with type 2 diabetes mellitus and atherosclerotic cardiovascular disease [48, 49].

Most importantly, the DAPA-HF trial with 4744 enrolled patients was the first study to show that the SGLT-2i dapagliflozin lowered the risk of worsening of heart failure or death from cardiovascular causes (primary composite study outcome) in HFrEF patients independent from the presence or absence of diabetes [5, 50] (for more details see also 3.4.1).

The currently ongoing trials (overview about finished and ongoing outcome trials are summarized by Lytvynt et al. [51] and Patel et al. [6]) will further reveal whether the cardio-protective effect of SGLT-2is is also present in HF-patients with preserved ejection fraction (HFpEF) [6].

Apart from the heart, the SGLT-2is were also shown to be reno-protective [52]. In this context, it has been recently announced by AstraZeneca that the ongoing DAPA-CKD trial [53] will be stopped early due to an 'overwhelming' efficiency [54].

Mechanistically, SGLT-2is were designed to primarily target the co-transporter for sodium and glucose in the renal proximal tubule and subsequently reduce their reabsorption in the kidney.

However, the potential mechanisms that mediate the cardio-reno-protective effects of SGLT-2is in HF patients are pleiotropic (Fig. 7) and currently intensively investigated and also debated as summarized in several recent reviews on this topic [4, 6, 51, 55-59].

#### 3.1.3.2 *SGLT-2i-mediated cardioprotection in heart failure- a 'volume-based' hypothesis*

Among the various proposed mechanistic hypothesis about the cardio-protective effect of SGLT-2is, the beneficial impact on volume regulation and body fluid balance has especially come into scientific focus. Indeed, a retrospective analysis of the EMPA-REG OUTCOME trial found that changes in markers related to plasma volume (e.g. Hct, Hb, albumin) were the most important mediators of risk reduction for cardiovascular deaths after the treatment with SGLT-2i in comparison with placebo [60].

As illustrated in Fig. 7 (blue squares) the treatment with SGLT-2is modulates fluid volume regulation in multiple ways. For example, the SGLT-2i dapagliflozin was shown to exert both natriuretic and osmotic diuretic effects in patients with type 2 diabetes and kidney damage [61]. Furthermore, it was proposed by use of mathematical modelling of data on plasma-/urinary sodium and water that dapagliflozin reduces the interstitial fluid volume relative to intravascular volume to greater extent than classical loop-diuretics, e.g. bumetanide [62].

Additional evidence comes from another recently published study in patients with diabetic kidney disease (DKD) [63]. The study results showed by use of bio-impedance analysis (BIA) that dapagliflozin treatment reduced intracellular (ICW)-, extracellular (ECW)- and total body water (TBW) in these patients after 1 week of treatment.

Importantly, the study authors found that only in patients with dapagliflozin treatment (in contrast to furosemide treatment) the baseline ECW/TBW correlated with the observed changes in ECW/TBW ( $r = -0.590$ ,  $p < 0.001$ ) and ECW ( $r = -0.374$ ,  $p = 0.025$ ) after 1 week of treatment. The study authors concluded that the effect magnitude of fluid volume reduction induced by dapagliflozin is dependent on the a priori 'volume-status' of the patient, suggesting that the drug effect is eventually more pronounced in patients with severe extracellular fluid retention than in patients with less, which further indicates a 'volume-stabilizing' effect of the drug.

Of note, Ohara et al. [64] reported in another work published previously that dapagliflozin treatment affected the fluid volume distribution in CKD patients differently than other classical diuretics such as furosemide, which further emphasizes the unique effects of SGLT-2is on the 'volume-status'.

Considering the above findings, the treatment with SGLT-2is might be in particular beneficial in HF

patients after being hospitalized due to an ADHF event as these patients are frequently present with 'subclinical' volume overload and congestion, especially within the interstitial fluid compartment, which potentially contributes to their high re-hospitalization rate after clinical discharge [7].

As also illustrated in Fig. 7, SGLT-2 inhibition has a dual effect on blood volume that is primarily mediated via the kidney. SGLT-2is reduce plasma volume and concomitant stimulate erythropoiesis [65, 66], which results in an increased oxygen transport capacity. Additionally, the SGLT-2is can lower albuminuria in HF patients [67], which leads to a reduced loss of the osmotic active proteins via the kidney and may help to maintain normal blood albumin levels and subsequently stabilize the volume distribution between the intravascular and interstitial fluid compartments.

Hypoalbuminemia is very common in HF patients and is associated with an increased risk of death [68, 69]. Here, a recent multivariate analysis showed that the serum albumin levels among other factors, e.g. blood pressure and hemoglobin concentration were independent predictors of long-term mortality in acute heart failure patients [70].

Another important volume stabilizing effect of SGLT-2is is their anti-inflammatory potential. As stated previously (see section 3.1.1.2), systemic inflammation also contributes to volume dysregulation and congestion in heart failure.

In this context, the inner layer of every vessel, named the endothelium and its function may play a central role. Endothelial dysfunction is a 'hallmark' of heart failure condition and associated with increased mortality [71, 72]. The endothelium not only controls the vessel wall diameter with its paracrine and endocrine secretory activity but also its integrity and permeability, which is crucial for fluid exchange between the intravascular and interstitial fluid compartment [73].

The anti-inflammatory effect of SGLT-2is in combination with the lowering effect on blood pressure protects the endothelium and its function, which may translate to an improved volume balance and distribution. Indeed, several studies found evidence for a beneficial effect of SGLT-2is on endothelial function [74].

In terms of relative plasma volume status (PVS), a recent a pooled data analysis in 4533 patients with type 2 diabetes showed that dapagliflozin decreased the estimated PV (ePV) by 9.6% compared to placebo after 12 months of treatment [75].

In the same study, the investigators could also show that the calculated ePV by use of the 'Strauss' formula correlated well with the actually measured PV (mPV) using the I-human serum albumin labelling method. The findings suggest that treatment with SGLT-2is can improve PVS, however it needs to be shown whether these findings can be translated to clinically stabilized HF patients after being hospitalized due to an ADHF event.

[figure not shown]

**Fig. 7: A schematic representation of the different mechanisms implicated in the cardiovascular benefits of SGLT2 inhibitors.** The blue squares underline the mechanistic structures affected by SGLT2-is with volume modulating potential (modified from Wojcik et al. [55]).

